**Statistical analysis**

Numerical data will be refined by excluding values beyond physiological limits. Data will be analysed using the statistical package R, with P values <0.05 being regarded as statistically significant. Expert statistical advice will be sought with the aim of using cox regression models to determine the association between serum phosphate and cardiovascular events, adjusting for the known cardiovascular risk factors. Cox proportional hazards multivariate models will also be constructed to provide a time-event analysis. A backwards stepwise elimination of variables approach will help to refine the model and evaluate the contribution of each variable towards the outcome measures.

Ethical considerations

Approval has been sought from the RCGP for the RSC database to be used for such research projects. Our study is retrospective and observational over anonymised patient data. The study involves no clinical interventions, no patient contact and no breach of confidentiality. The results of the study will be submitted for publication to a peer-reviewed journal.

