**Research question**

Is serum phosphate an independent predictor of new atherosclerotic cardiovascular disease events in patients stratified by renal function?

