**Data source and Sample Size**

RCGP-RSC data will be used for this study. These are from a database of coded primary care data from 135 UK General Practitioner (GP) practices – total population of approximately 1,250,000 patients. A large sample size is necessary for this study due to the variability in serum phosphate concentrations and the duration of the observational period (up to ten years).

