**Limitations**

The study population will only include patients that have had sufficient routine blood tests taken. This may introduce bias for increased risk of confounding co-morbidities amongst this group. Serum phosphate levels are influenced acutely and chronically by many factors including disease, exercise and diet - which independently influence cardiovascular risk. We aim to control for cardiovascular risk factors based on the QRISK2 model [6].

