**Intended output**

Outcome measure 1, 2 or 3 – each outcome requires its own table

|  | Outcome X | | |
| --- | --- | --- | --- |
| *Variable* | *Hazard ratio* | *95% CI* | *p value* |
| Age |  |  |  |
| Gender |  |  |  |
| Ethnicity |  |  |  |
| BMI |  |  |  |
| PDDS |  |  |  |
| Smoking |  |  |  |
| Syst. BP |  |  |  |
| HbA1c |  |  |  |
| Tot chol |  |  |  |
| LDL |  |  |  |
| HDL |  |  |  |
| Albumin |  |  |  |
| **Phosphate** |  |  |  |
| Calcium |  |  |  |
| Vit D |  |  |  |
| PTH |  |  |  |
| Sodium |  |  |  |
| Potassium |  |  |  |
| Albumin:Cr ratio |  |  |  |
| Baseline eGFR |  |  |  |

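### Backward elimination is a poor way to build Cox models meant to estimate one adjusted exposure effect, because neither phosphate nor the listed confounders are protected from removal

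*Protocol*

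**What the plan says.** The Research question asks about a single exposure: "Is serum phosphate an independent predictor of new atherosclerotic cardiovascular disease events in patients stratified by renal function". The Statistical analysis section repeats that aim. Cox models are to be used "to determine the association between serum phosphate and cardiovascular events, adjusting for the known cardiovascular risk factors". It then adds the selection step: "A backwards stepwise elimination of variables approach will help to refine the model and evaluate the contribution of each variable towards the outcome measures".

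No removal criterion is given. The only threshold is general, "with P values <0.05 being regarded as statistically significant". Neither phosphate nor any other variable is said to stay in the model regardless.

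Two other sections bear on this. Limitations says "We aim to control for cardiovascular risk factors based on the QRISK2 model", which is an adjustment set chosen in advance. Intended output says "each outcome requires its own table" and gives a shell with a hazard ratio, 95% CI and p value for each of 20 variables, phosphate in bold. The Background adds that calcium, vitamin D and PTH are to be studied together with phosphate.

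**The concern.** Elimination keeps a variable if it is itself clearly associated with the outcome. A variable can confound phosphate and still fail that test, if its own effect is weak but it is tied to phosphate. Dropping several such variables moves their combined effect into the phosphate coefficient. Phosphate is open to removal on the same terms, which would leave the row of main interest empty. The standard errors of the final model treat it as if it had been fixed in advance, so its intervals and p values are too optimistic.

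The adjusted phosphate hazard ratio for each outcome is at stake, most of all where events are few.

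**Working it through.** **Setting the sections side by side.** A model with a pre-chosen adjustment set, reported in a 20-row table, fills every row. A model after elimination has no estimate for a removed variable. Both cannot describe the same reported model, and the protocol does not say which one fills the table. There are seven outcomes (one composite, three cardiac, three non-cardiac), so elimination could leave seven different adjustment sets.

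**Size.** The protocol has no figure to reproduce. It gives the source population ("total population of approximately 1,250,000 patients") but not the number with phosphate measured, the events or any correlations. All inputs below are therefore assumptions, except the 20 terms (table rows) and p<0.05 (the only stated threshold).

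*Set-up.* Phosphate has no true effect. Six confounders, uncorrelated with each other, each have correlation r with phosphate and log hazard ratio b per SD. The other 13 terms are noise. The large-sample Cox approximation is used: information = events × correlation matrix.

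*Mechanism by hand, with r = 0.25, b = 0.05 and 1,000 events.*
- Full-model variance of a confounder's coefficient: [1 + r²/(1 − 6r²)]/events = [1 + 0.0625/0.625]/1,000 = 1.1/1,000, so SE = 0.0332.
- Expected z = 0.05/0.0332 = 1.51. The chance of passing 1.96 is about P(Z > 0.45) = 0.33. Each real confounder therefore fails the full-model test about two times in three.
- If all six are dropped, the phosphate log hazard ratio moves by 6 × 0.25 × 0.05 = 0.075, a hazard ratio of 1.08 per SD where the truth is 1. The SE is then 1/√1,000 = 0.0316, so z shifts by about 2.4.

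*Simulation.* Elimination at p<0.05, phosphate not protected, 1,000–2,000 replicates per setting; simulation error is about one percentage point.

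| r | b per SD | Events | Phosphate falsely significant |
|---|---|---|---|
| 0.25 | 0.03–0.08, same direction | 500–1,000 | 9–16% |
| 0.25 | 0.03, same direction | 3,000 | 16–19% |
| 0.25 | 0.03–0.08, same direction | 10,000 | 4–9%, highest at b = 0.03 |
| 0.25 | 0.20 | 500–10,000 | 4–6% |
| 0.05–0.10 | 0.03–0.20 | 500–10,000 | 4–7% |
| 0.25 | 0.03, mixed signs | 500–1,000 | 5–8% |

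The full model gives about 4–6% throughout.

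*Further results.*
- With no true effect, phosphate is removed in about 82–96% of runs at r = 0.25. When it stays, it stays because p<0.05, so its interval always excludes the true value.
- Keeping phosphate while still eliminating covariates is worse: 14–37% falsely significant at 500–1,000 events. Protecting phosphate alone is no cure.
- A softer rule does not remove the problem. With r = 0.3 and hazard ratio 1.08 per SD, p<0.05 gives 21%, 9% and 5% at 500, 2,000 and 10,000 events. An AIC-type rule (p<0.157 for one degree of freedom) gives 21%, 8% and 6%.
- In that same setting, with a true phosphate hazard ratio of 1.05 per SD and p<0.05, phosphate is removed in 58%, 62% and 9% of runs.

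**The case against.** The strongest reply is that the protocol never says the reduced model supplies the reported phosphate estimate. It speaks of adjustment for known risk factors, of QRISK2-based control and of a full 20-row table. Elimination could be an adjunct for looking at each variable's contribution. That reading is fair, and it limits the point: a reader might infer that the reported intervals and p values are invalid, but the text supports this only if they come from the selected model. It does not clear the protocol, because refining the model is the stated purpose of elimination and no other model is named as primary.

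Second, the size rests on assumptions. Six independent confounders at correlation 0.25 explain 6 × 0.0625 = 37.5% of the variance of phosphate; at 0.3 they explain 54%. These are strong links, and with weaker ones the inflation nearly vanishes. This stands.

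Third, the removal criterion, protected terms and expert statistical input could be settled in a statistical analysis plan that is not shown. This also stands: their absence is not the finding. The finding is the choice of elimination for this aim, which the protocol does state.

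Two other inferences fail. Hazard ratios adjusted for different variables would not be like for like across outcomes, but the protocol plans separate tables and no such comparison. And one minus the false-positive rate, 84–91% in the worst settings, is not interval coverage, because it counts runs with no phosphate interval as covered.

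**Conclusion.** The point holds as a poor stated method, in conflict with the protocol's own adjustment aim and table. It should be fixed before analysis. It does not show that the study's inference fails. Selection by p value is itself an inference from the general threshold, though the problem persists under an AIC-type rule.

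In the unfavourable illustration the false-positive rate for phosphate roughly doubles or triples, from about 5% to 9–16% at 500–1,000 events. This needs confounders that are weak for the outcome, clearly tied to phosphate and mostly acting in one direction. With about 10,000 events it largely disappears unless confounders are very weak. It therefore matters mainly for the rarer individual outcomes, for renal-function strata and for subsets with complete biochemistry such as PTH and vitamin D. Large numbers do not cure the conflict with the 20-row table.

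**What to change.** In Statistical analysis, state that the primary analysis for each outcome is one pre-specified Cox model containing phosphate and the same listed confounders, all kept regardless of p value. Report the Intended output table from that model. Assess each variable's contribution by likelihood-ratio or Wald tests within it. Delete backward elimination, or label it exploratory with no bearing on the reported phosphate estimate.

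The cost is a few lines of protocol text and somewhat wider intervals. Against a model that dropped all six confounders, the phosphate SE grows by 1/√(1 − 0.06) = 1.03 at correlation 0.10 and by 1/√(1 − 0.375) = 1.26 at 0.25; the narrower interval in the second case is centred on a biased value. Model size should not be an obstacle: 500 events over 20 terms is 25 per term, somewhat fewer if ethnicity and smoking take several categories.

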**Limitations**

The study population will only include patients that have had sufficient routine blood tests taken. This may introduce bias for increased risk of confounding co-morbidities amongst this group. Serum phosphate levels are influenced acutely and chronically by many factors including disease, exercise and diet - which independently influence cardiovascular risk. We aim to control for cardiovascular risk factors based on the QRISK2 model [6].

**Intended output**

Outcome measure 1, 2 or 3 – each outcome requires its own table

|  | Outcome X | | |
| --- | --- | --- | --- |
| *Variable* | *Hazard ratio* | *95% CI* | *p value* |
| Age |  |  |  |
| Gender |  |  |  |
| Ethnicity |  |  |  |
| BMI |  |  |  |
| PDDS |  |  |  |
| Smoking |  |  |  |
| Syst. BP |  |  |  |
| HbA1c |  |  |  |
| Tot chol |  |  |  |
| LDL |  |  |  |
| HDL |  |  |  |
| Albumin |  |  |  |
| **Phosphate** |  |  |  |
| Calcium |  |  |  |
| Vit D |  |  |  |
| PTH |  |  |  |
| Sodium |  |  |  |
| Potassium |  |  |  |
| Albumin:Cr ratio |  |  |  |
| Baseline eGFR |  |  |  |

